#### Discontinuation of the treatment/ disease progression

In case of biochemical progression (defined according to the EAU guidelines [13]) after SBRT, a new imaging scan should be considered: a WB MRI or Ch-PET/CT scan at time of biochemical progression or symptomatic progression and 6-montly afterwards until clinical progression will be performed. Further treatments (including ADT or other treatments according to the institutional policy) should not be started for biochemical progression without documented clinical progression on WB MRI or Ch-PET/CT. Repeated SBRT is allowed.

#### Ethical consideration and study registration

The study will be performed in accordance with the Declaration of Helsinki and will comply to the International Conference on Harmonization and Good Clinical Practice. All possible treatments and examinations for CRPC are undertaken after obtaining written informed consent from the patients before registration. This trial was supported by the research grants from the Italian Association for Cancer Research (AIRC) IG-22159.

The RADIOSA study was approved by the Ethics Committee of “IRCCS Istituto Europeo di Oncologia and Centro Cardiologico Monzino” (IEO-997).

The study has been registered at clinicaltrials.gov (NCT03940235).

#### Calculation of the target sample size

The main endpoint of this study is time to progression (local, biochemical and clinical progression) in oligometastatic PCA patients. We designed a randomized phase II selection study in which patients are randomized to two treatments and the results with the longest time to progression is selected for further study [12]. The aim is to compare time to progression between the two study arms: SBRT only or SBRT and hormonotherapy, with α = 0.10 and β = 0.20. It is estimated that the median delay to start palliative ADT after metastasis-directed therapy is approximately 24 months [17]. In order to detect a 12-month difference in the main endpoint from 12 to 24 months, a total of 152 patients will be needed, using a two-sided hypothesis based on the F distribution. Assuming a 5% rate of loss to follow-up, a total of 160 patients will be accrued over 36 months with 24 months of additional follow-up. We expect an accrual rate of 53 patients per year.

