**Fig. 1 Fig1:**
[figure not shown]
Study design

The patients will be randomized in either:
ARM 1: salvage SBRT for lymph nodes and/or bone metastases. All the radiologically documented lesions will be treated simultaneously.ARM 2: salvage SBRT (as described for ARM 1) + 6-month ADT (luteinizing hormone-releasing hormone (LHRH) agonist or antagonist). ADT should start within 1 week before the start of SBRT.

Phase 2 is complementary to Phase 1. After SBRT completion, patients will be followed-up with PSA and testosterone measurements every 3 months and with clinical examination at 3 and 6 months and every 6 months thereafter. Questionnaires for the assessment of QoL will be administered within 2 weeks prior to randomization, at 3 and 12 months, and yearly thereafter.

Blood and plasma samples for biological evaluation and randomization of patients, at 3 months from completion of treatment and at clinical relapse. The samples will be stored in the “European Institute of Oncology Biobank”.

Acute and late toxicity will be assessed according to the Common Toxicity Criteria for adverse events (CTCAE) toxicity criteria v4.3 [16], evaluated at 1 (acute toxicity) and at 3–6 months after the end SBRT and yearly afterwards (late toxicity). Time to castration-resistant disease will be assessed as time to start a systemic therapy (testosterone evaluation). A timeline of this study is summarized in Table 1.

**Table 1 Tab1:** Timeline of the study

	Screening	2 weeks within randomization	1 months after end of RT	3 months after end of RT	Every 3 months	12 months after end of RT	Every year	Biochimical relapse	Clinical relapse
Physical examination	x			x		x			
PSA/testosterone	x			x	x	x			
GS	x								
Previous treatments for PCa	x								
ECOG score	x								
Comorbidities	x								
Imaging	x								
Blood tests (NLR)		x							
Serum and plasma collection		x		x					x
Acute toxicity assessment			x						
Late toxicity assessment				x					
QoL		x		x		x	x		x
Cho-PET/TC or RM-WB								x	x

Moreover, a decision-tree algorithm, based on prognosis, imaging profile and biological phenotype will be developed: it will be addressed to identify recurrent PCa that remains oligometastatic and those that rapidly progress to a polymetastatic phase, thus allowing in the future to stratify patients who might avoid, or at least delay ADT, or not.

Data will be published at the end of the end of enrollment (2024).

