## Discussion

Recently, the concept of ADT-free survival, intended as the time to the delayed start of ADT, in order to spare the related negative side effect, such as the increased occurrence of cardiovascular events and metabolic syndrome, that significantly affect the QoL [7]. The aim of SBRT in this setting is to achieve local control and delay progression, and thereby postpone the need for further treatments.

From the clinical standpoint, the emergence of castration resistance is usually a nearby antecedent of widespread disease progression, visceral involvement and death from PCa. Therefore, preservation of the responsiveness to ADT is crucial in the long-term management of patients with metastatic PCa.

Also, from socio-economic point of view, 12 months without ADT can be considered a consistent gain for the National Health System, especially considering the relevant costs of the new and spreading anti-androgens like Abiraterone and Enzalutamide [5].

Current knowledge is mainly based on retrospective and non-randomized studies, thus suffering from heterogeneous population (i.e., due to biased patient selection) and inappropriate sample power [18].

It is evident that also in the setting of metastatic PCa, prostatic definitive radiotherapy could find a place. First data derived from retrospective trials by Löppenberg et al. and Rusthoven et al. demonstrated an improvement in OS for patients who underwent radiation therapy targeting the prostate in comparison to those who received only hormonal treatment [19, 20].

The oligometastatic concept has been developed in the last years and recent trials show interesting results on adding local treatments (LCT) (such as radiotherapy or surgery) at standard therapy. Particularly, it is important to mention the results achieved by Gomez and Palma. Gomez et al., that conducted a randomized phase II trial on oligometastatic NSCLC, reporting a significant PFS benefit with LCT (both radiotherapy or surgery) vs maintenance systemic therapy (14.4 months vs 4.4 months respectively) [18]. In another randomized phase II trial, named SABR-COMET, a benefit in OS in the SBRT arm for the oligometastatic setting compared to palliative treatment was demonstrated (41 months vs 28 months) [21].

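### The sizing's only cited input is a time-to-ADT figure, neither median is assigned to an arm, and 80% power with 152 patients does not follow from 12 versus 24 months

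*Protocol article*

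**What the plan says.** All of the sizing is in the protocol article, section Calculation of the target sample size.

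- Endpoint: "The main endpoint of this study is time to progression (local, biochemical and clinical progression) in oligometastatic PCA patients".
- Cited clinical input: "It is estimated that the median delay to start palliative ADT after metastasis-directed therapy is approximately 24 months".
- Effect and size: "In order to detect a 12-month difference in the main endpoint from 12 to 24 months, a total of 152 patients will be needed".
- Error rates and test: "with α = 0.10 and β = 0.20", "using a two-sided hypothesis based on the F distribution".
- Logistics: 5% loss to follow-up, hence 160 patients, accrued over 36 months and followed for a further 24.

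Three other places bear on it. The arm descriptions under Methods of recruitment and random allocation give "ARM 1: salvage SBRT for lymph nodes and/or bone metastases"; Arm 2 adds six months of ADT, starting within a week before SBRT. Endpoints of the study lists ADT-free survival as a secondary endpoint, apart from the primary. Discontinuation of the treatment/ disease progression says that further treatments, ADT included, "should not be started for biochemical progression without documented clinical progression on WB MRI or Ch-PET/CT. Repeated SBRT is allowed".

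**The concern.** The cited 24 months and the sized endpoint are different outcomes. Biochemical progression counts as an event in the sizing section, but in this trial it is not by itself a reason to start ADT, and repeat SBRT may come first. Here, then, time to ADT will generally be later than time to progression.

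The figure also describes patients who had metastasis-directed therapy and had not yet started palliative ADT. Those patients resemble Arm 1, not Arm 2. Yet 24 appears next as the upper end of the 12-to-24 range, with no arm named and no basis given for 12.

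At stake is how the result will be read. The ability to detect an effect of adding ADT depends on the SBRT-only median for progression. If that median is not pinned down, neither a null nor a positive result can be judged against the stated 80%.

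**Working it through.** **Inputs.** From the sample-size section: medians 12 and 24 months, two-sided alpha 0.10, power 0.80, F test, 152 patients (160 after loss), accrual 36 months, follow-up 24 months. From the recruitment section: 1:1 allocation, so 76 per arm. Assumed here: exponential times (implied by the F test), uniform accrual, and no censoring before the analysis among the 152.

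**Step 1. The plan's own figure.** The loss adjustment reproduces: 152/0.95 = 160. For the 152 itself, with r events per arm and median ratio R, power = P(F > c/R), where F has (2r, 2r) degrees of freedom and c is its 95th percentile.

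- R = 24/12 = 2: r = 26 gives 0.798 and r = 27 (c = 1.571) gives 0.811. So 54 events are needed in total. The Schoenfeld formula gives 4(1.645 + 0.842)²/(ln 2)² = 51.5, or 52.
- R = 1.5: r = 75 gives 0.797 and r = 76 (c = 1.307) gives 0.802. So 152 events are needed in total, exactly the printed number. Schoenfeld gives 151.

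A ratio of 1.5 with a 12-month difference fixes the medians: 1.5m − m = 12, so m = 24 and the pair is 24 versus 36. The printed 152 therefore matches an event count for 24 versus 36, and not the printed 12 versus 24.

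**Step 2. From events to patients.** For median m, with λ = ln 2/m, the probability of an event by the analysis is

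p(m) = 1 − [exp(−24λ) − exp(−60λ)]/(36λ).

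- p(12) = 1 − (0.2500 − 0.0313)/2.079 = 0.895
- p(24) = 1 − (0.5000 − 0.1768)/1.040 = 0.689
- p(36) = 1 − (0.6300 − 0.3150)/0.693 = 0.546

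For 12 versus 24, the 54 events need 54/[(0.895 + 0.689)/2], about 68 patients. For 24 versus 36, the 152 events need 152/[(0.689 + 0.546)/2], about 246 patients.

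**Step 3. Power with 152 patients for a 12-month gain.** Events per arm are d = 76·p(m). Power is from the F test with (2d₂, 2d₁) degrees of freedom.

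| Shorter median (SBRT-only taken as reference) | Longer median | Ratio | Events | Power |
|---|---|---|---|---|
| 12 | 24 | 2.00 | 120 | 98% |
| 15 | 27 | 1.80 | 113 | 93% |
| 18 | 30 | 1.67 | 106 | 83% |
| 20 | 32 | 1.60 | 102 | 76% |
| 24 | 36 | 1.50 | 94 | 62% |

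Power is 81% at a shorter median of 18.5 months and just under 80% at 19. The normal approximation ln R/√(1/d₁ + 1/d₂) agrees within 0.2 points on every row.

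**The case against.** The strongest reply is that the paragraph never says the cited 24 months is the better arm's median. It gives a background figure and then a difference, and assigns neither number. The printed 152 even suggests the opposite: it fits 24 versus 36, with 24 as the SBRT-only value in the arm it describes, and then the slip lies in the words about 12 to 24. This stands. A reader might infer that the figure was put in the wrong arm, but the documents leave its placement open. Nor does the match at 152 prove how the number was obtained.

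Four other tempting readings also go too far.

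- **That 24 months is an upper bound for SBRT alone.** The rule on starting ADT governs this trial. The rules of the cited study are not shown, so its figure cannot be bounded that way.
- **That the plan assumes no progression median, or powers a different contrast.** The section states 12 to 24 months in the main endpoint and attaches alpha and beta to SBRT versus SBRT plus hormonal therapy. What is missing is the link from median to arm.
- **That 12 months is wrong and the trial underpowered.** With biochemical progression in the endpoint, an SBRT-only median near 12 months is plausible, and power there is 98%. The 62% takes the time-to-ADT figure as a progression median, so it is the pessimistic end.
- **That the Discussion's remark, "12 months without ADT can be considered a consistent gain for the National Health System", is the basis for the 12-month difference.** It is a socio-economic comment and is not tied to the sizing.

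It can also be said that a target difference needs no literature source, that a condensed article may leave sources to the full protocol, and that in a two-sided selection design it does not matter for power which arm is longer. All are fair, and an unsourced 12 months alone would be a minor matter. They do not explain a printed sample size that fails to follow from the printed medians.

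**Conclusion.** The point holds in this limited form. The sizing rests on progression, but its only cited input is time to palliative ADT in patients treated like Arm 1, and the two medians are not assigned to arms. On the printed inputs the stated 80% power is not the design's power: 152 patients give about 98% for 12 versus 24 months, and about 62% for the 24-versus-36 pair that the F test links to 152. A shortfall is possible but not demonstrated. It arises if the SBRT-only median for progression is about 19 months or more and the target gain stays at 12 months.

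These figures assume exponential times, uniform accrual and 152 evaluable patients. The paragraph should be corrected; the trial need not be enlarged on this evidence.

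**What to change.** Keep 160 patients and rewrite the sample-size paragraph:

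1. State the assumed median time to progression for each arm, with the SBRT-only value set and justified on the trial's own progression endpoint.
2. Keep the 24-month time-to-ADT figure as background for ADT-free survival, or say explicitly that it serves as a proxy for progression.
3. Say whether 152 counts events or patients, and reconcile it with the printed medians.
4. Replace the single 80% with power over SBRT-only medians of 12 to 24 months for a 12-month gain: 98% at 12, 83% at 18 and 62% at 24, falling below 80% from about 19 months.

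The cost is one reworded paragraph, with no added patients or procedures. The drawback is that the stated power becomes a range, part of which lies below 80%.

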#### Methods of recruitment and random allocation

In phase 1 a hundred sixty consecutive patients will be enrolled at the Division of Radiation Oncology at the European Institute of Oncology (IEO), Milan, Italy within a multidisciplinary uro-oncology board.

There will be a 1:1 randomization between Arm 1 and Arm 2. Patients will be stratified according to PSA doubling time (≤3 vs. > 3 months) [14, 15], initial localization of metastases (node vs bone) and diagnostic imaging (PET vs. MRI) [Fig. 1].

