The HORRAD study is a multi-centric prospective study, randomized controlled trial recruiting bone metastatic PCa patients. The objective was to compare irradiation of primary prostatic tumor with external beam radiation therapy with ADT versus ADT only. The trial revealed no significant difference in OS. However, subgroup analysis suggests that radiotherapy to the prostate actually improves OS in patients with a low metastatic burden (< 5 bone lesions) [22].

More recently, subgroup analysis of patients with a low metastatic burden from STAMPEDE (a phase 3 randomized controlled trial) showed that OS was improved with radiotherapy, giving a three-year survival of 81% in these men, compared to 73% in the standard treatment group [5].

For Murphy et al., the approach to metastatic PCa “catching ‘em all”, or “pokemet”, must be considered experimental [23]. Also, in this setting, data from retrospective studies suggest that cancer specific and OS is improved with Metastasis-directed therapy (MDT) compared to the standard of care. MDT treatment regimens vary with different radiotherapy techniques, doses, and volumes [3]. Among prospective studies, STOMP and ORIOLE trials are worth mentioning [24, 25].

However, despite encouraging data, some authors remain skeptical that MDT will delay the use of ADT. Moreover, this argument is a weak endpoint compared to PFS or OS especially given that timing for using hormonotherapy remains controversial.

Whereas the use of systemic therapy was largely investigated by several large clinical trials, currently, limited studies focus on metastasis-directed SBRT. These studies, despite short follow-up that limited the evaluation of OS and cancer-specific survival, showed that metastasis-directed SBRT is a safe treatment, reaching a high local control (about 95%) with low-grade toxicity, generally limited to gastro-intestinal effects [3, 26–29].

So, new biomarkers are mandatory to help determining the natural history of the disease and to select the patients who could actually benefit from MDT. The discovery of miRNA seems to give a start of answers to many questions that arise.

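### The 152 patients do not follow from 12 versus 24 months: that hypothesis needs 54 events, and the stated 80% power holds on none of the readings examined

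*Protocol article*

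**What the plan says.** All the inputs stand in the protocol article, mostly in the section on calculating the target sample size.

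- The main endpoint there is time to progression, counting local, biochemical and clinical progression.
- Error rates and test: "with α = 0.10 and β = 0.20", "using a two-sided hypothesis based on the F distribution".
- The one referenced time: "It is estimated that the median delay to start palliative ADT after metastasis-directed therapy is approximately 24 months".
- The hypothesis and the size: "In order to detect a 12-month difference in the main endpoint from 12 to 24 months, a total of 152 patients will be needed".
- A 5% loss to follow-up raises the total to 160, accrued over 36 months with 24 months of additional follow-up.
- Allocation, from the section on recruitment and random allocation: "There will be a 1:1 randomization between Arm 1 and Arm 2".

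No number of events is given. The section on endpoints words the primary endpoint differently, as progression-free survival meaning absence of new metastatic lesions, and lists biochemical progression-free survival and ADT-free survival as separate secondary endpoints.

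**The concern.** A doubling of the median is a large effect, and 152 is far more than a time-to-event comparison of that effect needs at these error rates. Either the medians or the size must therefore be misstated. Two further features point to a faulty derivation. The F test for exponential times counts events, yet its result is given as patients. The only referenced median concerns time to starting palliative ADT, not time to progression, and no source is given for the 12 months.

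The trial is meant to choose which arm goes forward to phase III, so the stated power governs how a null result is read. If the design is really aimed at a ratio of 1.5, a null result would be taken as an 80%-power negative when the power was lower. If it is aimed at 12 versus 24 months, readers are misinformed about how small an effect the trial can detect.

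**Working it through.** **Inputs (all from the article):** two-sided alpha 0.10; power 0.80; 1:1 allocation; medians 12 and 24 months; 152 evaluable patients; 36 months of accrual plus 24 months of follow-up. **Assumptions added here:** exponential times, uniform accrual, analysis at 60 months.

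**Step 1: the inflation step.** 152 / 0.95 = 160. This reproduces.

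**Step 2: events needed.** With d events per arm and a ratio r of medians, the ratio of estimated mean times is distributed as r × F(2d, 2d). Let c be the 95th percentile of F(2d, 2d). Power is P(F > c/r), the other tail being negligible.

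- r = 2 (12 versus 24): d = 26 gives 79.8% and d = 27 gives 81.1% (c = 1.571, c/r = 0.785). The requirement is 27 per arm, **54 events**. The Schoenfeld and Freedman formulas give 52 and 56.
- r = 1.5: d = 75 gives 79.7% and d = 76 gives 80.2% (c = 1.307, c/r = 0.871). The requirement is 76 per arm, **152 events**, the article's figure exactly. Schoenfeld gives 151 and Freedman 155.

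**Step 3: can 152 be reached from 12 versus 24 another way?** At alpha 0.10 or 0.05 and 80% or 90% power, one- or two-sided, the largest event count is 95. With no minimum follow-up the stated settings still need only about 113 patients. Comparing 12-month progression-free proportions (50% versus 70.7%) with a continuity correction gives 156. That is close, but it is not 152 and not the stated method.

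**Step 4: events expected on the planned calendar.** For median m in months, the probability of an event by the analysis is

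p(m) = 1 − [m / (36 ln 2)] × (2^(−24/m) − 2^(−60/m)).

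This gives p(12) = 0.895, p(18) = 0.785, p(24) = 0.689 and p(36) = 0.546. With 76 patients per arm, and expected events used as the degrees of freedom in the F calculation:

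| Medians (months) | Ratio | Expected events from 152 patients | Power |
|---|---|---|---|
| 12 vs 24 | 2.0 | 68.0 + 52.4 = 120.4 | 98% |
| 12 vs 18 | 1.5 | 68.0 + 59.7 = 127.7 | 74% |
| 24 vs 36 | 1.5 | 52.4 + 41.5 = 93.8 | 62% |

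A log-rank simulation of 4,000 trials gave 98.9% for the first row and 62.1% for the last. With all 160 patients followed, 24 versus 36 gives about 99 events and 64% power.

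**Step 5: what the design can do.** For 12 versus 24, 80% power needs 68 patients (54 / [(0.895 + 0.689) / 2] ≈ 68). With 152 patients and a shorter median of 12 months, 80% power is reached at a longer median of 18.7 months, a hazard ratio of 12 / 18.7 ≈ 0.64. For 24 versus 36, 80% power would need about 248 evaluable patients.

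**The case against.** **Taken literally, the trial is not short of power.** On 12 versus 24 months it has about 98%, and a test with more power than stated is still valid. That stands. The error in that case is in the stated figures, and the harm is confined to misinforming readers about the detectable effect.

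**A reader might infer that 24 versus 36 months was the real hypothesis, so that the trial simply has 62% power.** The neighbouring 24-month figure plus a 12-month difference makes this a reasonable guess, but 36 months is nowhere mentioned as a median and any ratio of 1.5 gives 152. For 12 versus 18 the power is about 74%. The 62% also takes 24 months as a median for progression, whereas the article gives it for start of ADT. The section on discontinuation says further treatment should not start for biochemical progression without documented clinical progression. Progression as the sample-size section defines it should therefore tend to come before ADT. A shorter progression median would mean more events than 94, so 62% may be pessimistic.

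**A reader might also infer that the 24 months describes the SBRT-only arm and has been put on the wrong side of the comparison.** The article says only that it follows metastasis-directed therapy. It does not say whether systemic therapy was given as well, and the Background section describes local treatment with or without it. The text does not support assigning the figure to an arm.

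**The selection-design label might seem to excuse the arithmetic.** It does not, because the paragraph states alpha, beta and a two-sided hypothesis. Nor is this a detail that an article leaves to the full protocol: the method, error rates, effect and size are all printed, and they disagree.

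**Conclusion.** Wrong as written. At the stated error rates and with the stated test, 152 is close to three times the 54 events that 12 versus 24 months requires, and more than twice the roughly 68 patients. This conclusion rests on the article's own inputs and does not depend on guessing the intended medians.

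That 152 is an event count for a ratio of 1.5 carried over as a patient count is a well-supported inference, because the match is exact under the article's own method. It yields 80% power only if every one of the 152 patients is observed to progress. Under exponential times, uniform accrual and analysis at 60 months, the stated 80% is too low for 12 versus 24 (about 98%) and too high for a ratio of 1.5 (about 62% to 74% over the two pairs of medians examined). It is correct for none of the three. The size of any power shortfall stays conditional until the authors state their medians.

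**What to change.** Keep the 160 patients and rewrite the sample-size paragraph.

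1. Reconcile the primary endpoint first: the endpoints section and the sample-size section define it differently, and a median cannot be stated until one definition is fixed.
2. State the median assumed in each arm on that endpoint, with its source. Time to start of ADT should not stand in for time to progression without a stated justification.
3. State the required number of events, the number expected at 36 + 24 months, and the power that results. Examples with 152 evaluable patients: 12 versus 24 months, 54 events required, about 120 expected, power about 98% (80% at a hazard ratio of about 0.64); or 24 versus 36 months, 152 events required, about 94 expected, power about 62% (64% if all 160 are followed).
4. Delete the statement that 152 patients correspond to 12 versus 24 months at beta 0.20.

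The cost is wording in the protocol and analysis plan, with no extra patients. If the intended ratio is 1.5, the price is a less favourable power statement. Should the authors want 80% for 24 versus 36 months, that is a different decision: about 248 evaluable patients (262 with 5% loss), or follow-up continued until about 152 events, which with 160 patients means nearly all of them.
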